## Abstract

**Background:**

Childhood immunisation coverage is very low in Nigeria (31%) with Zamfara State being amongst the states with the poorest coverage (<10%). Lack of maternal knowledge, attitude, outcome expectations, self-efficacy, cultural beliefs and assumptions of religious regulations of antenatal mothers towards childhood immunisation are the contributory factors to poor childhood immunisation uptake. This study aims is to develop, implement and evaluate the effects of an immunisation health educational intervention with application of Social Cognitive Theory on pregnant women to improve knowledge, attitude, outcome expectations, self-efficacy, cultural beliefs and assumptions on religious regulations regarding childhood immunization uptake in Federal Medical Centre Gusau, Zamfara State, Nigeria.

**Methodology:**

The study will be a single-blind parallel-group randomised controlled trial, where baseline data will be collected from 392 estimated antenatal mothers, after that they will be evenly randomised using randomly generated permuted block sizes (each containing two intervention and two control assignments). The study participants will be antenatal mothers of ages 18 years and above who are in third trimesters and attending Federal Medical Centre Gusau, Zamfara State, Nigeria; during the study period and fulfilled all the inclusion and exclusion criteria. The intervention group will undergo five-health education sessions on immunisation, which will be strictly guided by Social Cognitive Theory-based intervention module: while the control group will receive usual care (standard care). Follow-up data will be collected using the same questionnaire at 6-weeks post-delivery, 10-weeks post-delivery and 14-weeks post-delivery. The generalized linear mixed model will be carried-out to determine the overall effect of the intervention after controlling for 14 potential confounding variables. An intention to treat analysis will also be carried-out. Childhood immunisation uptake is the primary outcome while the secondary outcomes are: improved knowledge scores, attitude scores, outcomes expectation, self-efficacy scores, cultural beliefs scores and assumptions on religious regulations scores.

**Discussion:**

The study will be a randomised controlled trial, that focuses on the effects of an immunisation health educational intervention with application of Social Cognitive Theory on pregnant women to improve knowledge, attitude, outcome expectations, self-efficacy, cultural beliefs and assumptions on religious regulations regarding childhood immunisation uptake in Federal Medical Centre Gusau, Zamfara State, Nigeria.

**Trial registration:**

Pan African Clinical Trial Registry PACTR202006722055635. Protocol registered on 09 June 2020.

## Background

The immune system of children is stimulated by vaccines to fight against diseases or infections. It is a well-established fact that immunisation is a tool that can effectively control and eradicate life-threatening infectious diseases [1]. Immunisation is considered as one of the most successful and cost-effective public health sustainable interventions for human beings against diseases that affect our health [2]. Routine immunisation plays an important role in reduction of child mortality, resulting from vaccine preventable diseases (VPDs). WHO revealed that immunisation has been estimated to prevent 3 million deaths globally every year [3].

Despite the efforts made by health organizations to combat diseases, vaccine preventable diseases have remained the most common cause of childhood mortality, which is estimated at 3 million deaths around the world annually [4]. In Nigeria, VPDs accounted for 17% and 22% of under‐five childhood morbidity and mortality respectively [5].

In Nigeria, routine vaccination coverage for all recommended vaccines has remained poor. However, there was an increase in vaccination coverage from 25.4% of eligible children (12–23 months of age) in 2013 to 31% in 2018 [6]. In Zamfara State, only 7.4% of the children are fully immunized [6]. Table 1 shows the individual vaccine uptakes comparing Zamfara state with Nigeria. According to the Expand Program on Immunisation (EPI), every child in Africa must receive one dose of Bacillus Calmette Guerin (BCG), Oral Polio Vaccine (OPV0) and Hepatitis B Vaccine (HBV1) at birth, Penta1 & OPV1 at 6 weeks of age, Penta2 & OPV2 at 10 weeks of age, Penta3 & OPV3 at 14 weeks old and measles and yellow fever at 9 months old [6].

**Table 1 pone.0263436.t001:** Individual vaccine uptakes.

Vaccines	BCG	DPT1	DPT3	OPV3	Measles
Nigeria	66.7%	65.3%	50.1%	47.2%	54%
Zamfara State	16.1%	17.1%	10.8%	15.2%	12.2%

Nigeria Demographic and Health Survey 2018 [6]

The World Health Organization (WHO) uses diphtheria, pertussis and tetanus (DPT3) coverage to monitor immunisation system performances across the districts of a country or territory. It indicates that a child has access to immunisation services and that the services were utilised; that is, they returned on at least 3 occasions [7]. The coverage for DPT3 vaccine varies across the states, for-instance, in Zamfara State only 10.8% of the children received the DPT3 vaccine, whereas at national level 50.1% of the children received the DPT3 vaccine [6]. These coverages are still far below the targets endorsed by WHO in 2012 Global Vaccine Action Plan, which aimed at ensuring delivery of universal access to immunisation with associated targets of reaching 90% national vaccination coverage and at least 80% vaccination coverage in every district [8].

Many observational studies conducted in Nigeria and other countries that focused on examining the factors influencing childhood immunisation uptake has discovered some personal factors: parental sociodemographic factors [4, 9–30], obstetric factors [10, 12, 15, 18, 25–29, 31–33], maternal knowledge gaps [10, 12, 13, 16, 20, 23, 25, 31, 34–38], maternal attitudes and self-efficacy [12–14, 36, 39–43], maternal outcome expectations [14, 35, 44–46]; environmental factors: physical and social factors influencing childhood immunisation uptake [18, 20, 22, 41, 47–52].

Despite the consistent poor childhood immunisation uptake, inadequate knowledge of mothers towards childhood immunisation is another considerable factor that has over the years contributed to poor attitude and practices of mothers towards childhood immunisation uptake among Nigerian mothers. Based on the literature search, only two health education intervention studies were conducted on increasing childhood immunisation uptake and both used a community based randomised-controlled trial. The first study was a controlled community trial conducted in Sokoto State, Nigeria which focused on evaluating the impact of immunisation health education intervention using Community Level Nutrition Information System for Action (COLINSA) strategy on knowledge and practice of childhood immunisation among mothers‘.’ At the end of the study, the proportion of children in the intervention group who received DPT1 was 35% and DPT3 33% while in the control group DPT1 was 25% and DPT3 was 20%. However, this finding is not statistically significant p = 0.734 [53].

The second study which was a randomised controlled trial, was carried-out to evaluate the effect of a low-literacy immunisation promotion educational intervention in improving DPT/Hepatitis B vaccine uptakes among 366 mother-infant pairs with infants aged ≤6 weeks of age in Karachi, Pakistan. At four months after enrolment, among 179 mother-infant pairs in the intervention group, 129 (72.1%) had received all the 3 doses of DPT/Hepatitis B vaccine while in the control group only 92/178 (51.7%) received all the 3 doses. This finding was statistically significant (ARR = 1.39; 95% CI: 1.06–1.81) [54]. However, none of the studies was guided by any health theory in providing a strategy and a step-by-step summary of specific factors to be considered when developing, implementing, and assessing the health education interventions. Notwithstanding the usual health education given to pregnant women attending antenatal at FMC Gusau, child immunisation uptake is still low. It is important therefore, to compare the results of our intervention group and that of control group to help in evaluating the effectiveness of the intervention.

Therefore, there is a need to develop and implement a theory-based intervention with application of social cognitive theory to evaluate the effectiveness of immunisation health education in improving the knowledge, attitude, outcome expectation, self-efficacy; cultural beliefs and assumptions on religious regulations of antenatal mothers which will hopefully increase childhood immunisation uptake and decrease mortality and morbidity among children in Nigeria. The intervention module that will be developed from this study may be adopted and consolidated into the routine health education delivering to pregnant women at the time of their antenatal care visits. This will provide better knowledge to antenatal mothers concerning the importance of child immunisation. The study findings could benefit policy makers in making decisions and formulating appropriate guidelines and policies with regards to childhood immunisation uptake in order to reduce childhood mortality and morbidity of VPDs. Other researchers may also adopt the validated questionnaire and intervention modules that will be developed from this research for future studies.

The research questions of this study are as follows:

What is the effect of an immunisation health educational intervention on the knowledge, attitude, outcome expectation, self-efficacy, cultural beliefs and assumptions of religious regulations among pregnant women attending Federal Medical Centre Gusau, Zamfara State, Nigeria?What is the effect of an immunisation health educational intervention on childhood immunization uptake in Federal Medical Centre Gusau, Zamfara State, Nigeria?

The proposed study will be single-blind parallel-group randomised controlled trial and will be guided using CONSORT Statement [55]. The participants will be randomised into either the intervention group which will received the SCT based health educational intervention on childhood immunisation, or the control group which will receive usual care (standard care).

### Trial aims and objectives

The aim of this randomized controlled trials (RCT) is to develop, implement and evaluate the effects of an immunisation health educational intervention with application of Social Cognitive Theory on pregnant women to improve childhood immunisation uptake among children in Federal Medical Centre Gusau, Zamfara State, Nigeria.

### Specific objectives

The specific objectives of this study are:

To determine and compare the baseline of respondents between intervention and control group at baseline according to:
Parental socio-demographic characteristics (maternal age, maternal education, paternal education, maternal marital status, maternal occupation, area of residence, number of siblings, religion, ethnicity and family income).Obstetric history (antenatal care follow-up, Maternal Tetanus Toxoid (MTT) vaccine and preceding birth intervals).Knowledge scores on (immunization, knowledge on VPDs and knowledge on EPI schedule).Outcome expectation scores (benefit of immunization and seriousness of VPDs).Attitudes scores (maternal perceptions towards childhood immunization).Self-efficacy scores (vaccine safety and vaccine side effect).Environmental factors (assumptions of religious regulations scores, cultural belief scores, distance to health facility, mode of transportation, hospital accessibility and attitude of hospital staff).To develop and implement an immunization health educational intervention based on Social Cognitive Theory for pregnant women in Federal Medical Centre Gusau, Zamfara State, Nigeria.To compare the total immunization knowledge, attitude, outcome expectation, self-efficacy, cultural beliefs and assumptions of religious regulations scores within the intervention and control group at baseline to 6-weeks post-delivery, 10-weeks post-delivery and 14-weeks post-delivery.To compare the knowledge, attitude, outcome expectation, self-efficacy, cultural beliefs and assumptions of religious regulations scores between the intervention and control group at baseline to 6-weeks post-delivery, 10-weeks post-delivery and 14-weeks post-delivery.To determine the effects of the intervention on improving child immunization uptake in Federal Medical Centre Gusau, Zamfara State, Nigeria.

## Methods

The study protocol was developed in accordance with Standard Items Recommendations for Interventional Trials (SPIRIT) guidelines [56] and it has been registered on 09 June 2020 with Pan African Clinical Trial Registry PACTR202006722055635 *(Refer to S1 Checklist).*

### Study design

The study will be single-blind parallel-group randomized controlled trial. The participants will be randomised into either the intervention group which will received the SCT based health educational intervention on childhood immunisation, or the control group which will receive usual care (standard care).

### Study setting and sampling population

The study setting will be Federal Medical Centre, Gusau Zamfara State, Nigeria. The sampling population of this proposed study will be pregnant women who will attend the hospital during the recruitment period. The study participants will be selected to participate according to pre-defined inclusion and exclusion criteria of the protocol.

### Eligibility criteria

The eligibility criteria for inclusion into the study will be as follows:

Antenatal mothers of age 18 years and above who are in third trimesters (28–35 gestational weeks); mothers with single pregnancy; must be mothers who planned to deliver and intended to attend the clinic to immunise their children at Federal Medical Centre Gusau; citizens of Nigeria and those resident in Gusau.

The following will be excluded from the study:

Mothers without good understanding of Hausa language as the intervention will be delivered in Hausa language; mothers who attended previous health education intervention on immunization will be excluded to minimise confounding; mothers living in the same household to minimise contamination; mothers of family with nomadic lifestyle will also be excluded as previous study revealed low immunisation uptake among children whose mothers’ practice nomadic lifestyle [20].

### Randomisation

Random assignment of the participants will be done on the same day that the participants will be selected into the study; the participants will be randomised to either the intervention (Immunization Health Education Intervention) or control group (usual care). However, it will be carried out before taking the baseline date.

### Sample size determination

The minimum sample size required to test the proposed study hypotheses has been determined using the formula for comparing two proportions in selected samples of both intervention and control groups [57]. This formula gave the required number (n) for each group. This provided a total sample size of 196 participants in each group, which will then be multiplied by two since the study is comprised of two arms. Therefore, 392 are the calculated sample size required to test the hypothesis for this study *(Refer to S1 File).*

### Random selection

In this study, the participants will be recruited within the eight succeeding booking sessions, which will hopefully provide a total sampling frame of 800 clients. The study participants will be selected using systematic random sampling technique from the sampling frame; K^th^ element of two will also be applied (800 divided by the sample size of 392). One of the first two eligible clients on the list will be selected using the table of random numbers. Afterwards, the selection of the second client will be made serially using the list until the last eligible client is selected. Based on the same sequence in the sampling frame, the list of participants will then be organized, with serial numbers assigned to them for the purpose of identification. Subsequently, the use of these serial numbers will be employed in random allocation for both groups. The sampling frame list will be prepared and provided by the hospital staff working in the Medical Records Department. Likewise, the recruitment based on the table random numbers will be performed by the hospital nurse from Antenatal Care Department. Both of them will not be participated in any of the study process.

### Sequence generation

In the current study, sequence generation will be performed by the hospital staff working in the Medical Records Department. The staff will be trained to perform the sequence generation. However, these staff will not be part of any process for this proposed research. A permuted block randomization technique, having equal size permuted blocks of four (each containing two for interventions and two for control group) will be used. Since the calculated sample size for this study is three hundred and nighty two, 98 permuted blocks will be required. Nevertheless, in order to avoid the problem of under-sampling, a little higher than the calculated sample size will be targeted for recruitment [58]. Thus, 110 permuted blocks containing all the possible combinations (for example; BABA, ABBA, AABB, ABAB, BBAA, BAAB) will be generated using the random function in Microsoft Excel.

### Allocation concealment mechanism

Opaque envelopes will be used to place in the sequences that will be generated and the medical records’ staff that will generate the sequence will then seal them. In order to guide the people responsible for the allocation the envelopes will also be serially numbered from the outside.

### Implementation

Two staff of the antenatal care unit will assist in assigning groups to the participants independently. The first staff will hand over the sealed envelopes to the participants in a serial order, and afterwards, the staff will be asked to match the serial numbers on the allocation envelopes with the participants’ given serial numbers succeeding the random sampling. Subsequently, the participants will be directed to the second staff, who will then open the envelopes and inform them of the date to come for their health education session based on the group they fall under. After this is done, the group to which the participant belong to, will be documented on a sheet provided. All the study participants will be given a hand card, which is the study pro forma containing the child’s serial number and bio-data. Also, the hand card will contain a short note that shows they have been enrolled into a follow-up study, and seeking any of the attending medical staff (nurse) to kindly assist in completing the post-natal findings as indicated on the card.

### Blinding

The proposed study will be single-blinded; the study enumerators will be blinded against the participants’ groups. In any of the processes either the group allocation, or delivering of the intervention, the enumerators will not be involved, and the participants’ groups will also not to be specified on their cards. The staff that will document the list of the assignment will keep it confidential, the staff will also be aware of the group coding (A and B), however, the staff will be unaware of the interventions that will be assigned to them.

### Intervention

The participants in the intervention group will receive the ‘‘Immunisation Health Education Intervention” while the participants in the control group will receive ‘‘usual care”. The proposed interventions will be implemented at 35 gestational weeks after the baseline data has been collected from the participants. Based on the recommendation of McMillan [59], educational interventions should be carried out using approaches that are in accordance with what is used in practice. It is based on this, that the delivery of educational interventions in this study will be done at group levels in a two session. Every session will be composed of forty participants, while the facilitator of each of the sessions will be a midwife nurse.

The process of module delivery will be closely monitored and supervised by the investigator, and the relevant feed-back will be given to the facilitator in order to ensure that the module is followed accordingly. The five modules will be delivered by the facilitator, who will ensure that the participants are actively engaged. It is estimated that the delivery sessions will last for 30 minutes, 30 minutes, 30 minutes, 1 hour, 30 minutes, 45 minutes, 1 hour and 30 minutes. For modules 1, 2, 3, 4 and 5 respectively *(Refer to S2 File)*. The participants will be allowed to take short breaks of about 10 to 15 minutes between modules. Each participant will be given the chance to demonstrate what she has learnt, and corrective feed-back will be provided at the end of the modules. A compensation fees of (500 Naira) approximately 1.2 USD will be given to the participants in the intervention group in favour of their transportation. The mothers in the intervention group will also be receiving a mobile call reminder at 7 days and 1 day before their childhood immunisation schedule. The participants in the control group will not receive any mobile call reminder. Any mother in either the intervention or control group who completed her child vaccination from 0-doses to penta-3 will receive a baby pampers at the end of the intervention which will cost N700 (Naira) approximately 1.5 USD as recommended by Bandura’s [60].

The usual care (standard care) given to antenatal mothers attending FMC Gusau will comprised of general lectures regarding birth preparedness, danger signs in pregnancy, malaria complications, preventions and treatments, breast feeding, postnatal check-up, immunisations, family planning and interactive sessions. These general lectures are always given to antenatal mothers during every visit which last for about two hours.

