#### Training of the module facilitator

The modules will be delivered by a midwife, who will also serve as a facilitator at all the health education sessions during antenatal visits. The researcher shall deliver a one-time one-on-one training session to the facilitator. The training session, which will involve teaching the midwife how to deliver the contents to the respondents, will last for about 4 hours. Before the midwives start delivering the modules, another session will be held to revise what they were taught in the previous session, so as to ensure that they are properly equipped to deliver the modules.

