In order to determine within-group differences with time for knowledge scores, attitude scores, outcome expectation scores, self-efficacy scores, cultural beliefs scores and assumptions of religious regulations scores the researcher will conduct one-way repeated measures analysis of variance (ANOVA) for these variables if there is no substantial non-normality of the residuals. Intention-to-treat analysis (ITT) will be carried-out separately for each group and replacement of missing data will be done through using multiple imputations technique. The estimated outputs that will be obtained after ITT analysis will then be pooled into a single data set, after that, the Generalized Linear Mixed Models (GLMM) analysis will be carried-out to investigate the overall effectiveness of the intervention using 95% Confidence Interval (CI) and 0.05 will be set as the level of significance. Two measures of effect size will be used in this study: Partial Eta squared and the coefficients of the fixed effects. Partial Eta squared will be used in the mixed design repeated measures ANOVA, and will be classified as small, medium or large effect (0.2, 0.5 and 0.8) respectively according to the magnitude. The coefficients of the fixed effects will be used in the GLMM analysis.

In order to check the robustness of the result, sensitivity analysis will be performed to determine the effect of drop out and non-response on the findings of the proposed study, the GLMM analysis will be repeated again without replacing the missing values. The differences between the coefficients obtained after replacement (intention to treat analysis) and before replacement of the missing values (per-protocol) will then be calculated and expressed as percentages of the former.

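### Education is given to interactive groups of forty, but the described sample size and t-tests allow for no session clustering and the GLMM does not name session

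*Protocol article*

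**What the plan says.** **Delivery.** The protocol article's Intervention section says that "the delivery of educational interventions in this study will be done at group levels in a two session". It adds: "Every session will be composed of forty participants, while the facilitator of each of the sessions will be a midwife nurse". The same section describes active engagement, a chance for each woman to demonstrate what she has learnt, and corrective feedback. The section on training of the module facilitator says: "The modules will be delivered by a midwife, who will also serve as a facilitator at all the health education sessions during antenatal visits"; it later uses the plural for midwives. The Abstract speaks of five education sessions.

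**Control arm.** Usual care consists of general lectures and interactive sessions. The article says: "These general lectures are always given to antenatal mothers during every visit". No fixed control groups are described.

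**Allocation.** Individual women are allocated 1:1 in blocks of four (Sequence generation). The Study process section reports 382 women randomised equally, which is 191 per arm.

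**Sample size.** The required number "has been determined using the formula for comparing two proportions in selected samples of both intervention and control groups", giving 196 per arm and 392 in total. The detail is in S1 File, which is not shown.

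**Analysis.** Between-group score comparisons use the independent t-test. For the GLMM, the "analysis will be carried-out to investigate the overall effectiveness of the intervention using 95% Confidence Interval" and a 0.05 significance level; the Abstract adds adjustment for 14 potential confounders. No random effect is specified, and no section names the education session as a factor in any analysis.

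**The concern.** Women who sit through the same interactive session share its discussion, its date and the way the modules were delivered that day. Their later scores and vaccination behaviour may therefore be more alike than those of women from different sessions. With individual randomisation and grouping in one arm, this is a partially nested design. An analysis that ignores the grouping counts correlated women as independent and understates the variance in the intervention arm.

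At stake are intervals that are too narrow, and tests that reject too often, for the primary outcome and the six secondary scores. The effective size is also smaller than the head count suggests. Because the groups are large, even a small ICC has a visible effect.

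**Working it through.** **Inputs**
- Group size m = 40 (Intervention section).
- Women per arm: 196 planned (Sample size determination), 191 allocated (382/2, Study process).
- Significance level 0.05 (Data analyses). Sidedness is not stated; two-sided is assumed.
- ICC: not given. Assumed range 0.01, 0.02, 0.05, with 0 as reference.
- Clustering in the intervention arm only: assumed.

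**The plan's own figure.** The article does not state the rates, power, sidedness or dropout behind 196, so the figure cannot be strictly reproduced. Borrowing 33% vs 20%, the DPT3 rates of the Sokoto community trial cited in the Background, with two-sided 5% and 80% power, the pooled formula gives 180 per arm. With continuity correction it gives 195. Two other routes also land nearby: the unpooled formula with a 10% loss allowance (177/0.9 = 197), and one-sided 5% with 90% power (196). The route is not identified, but 196 can be reached without any design effect.

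**Effect of ignoring session**
- Design effect in the intervention arm: DE = 1 + (40 − 1) × ICC.
- Variance ratio of the difference, with equal arms and similar variances: R = (DE + 1)/2.
- Factor by which the SE is understated: √R.
- Actual level of a nominal 5% test: 2 × [1 − Φ(1.96/√R)].
- Effective intervention n: 191/DE.

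| Assumed ICC | DE | R | √R | Actual level | Effective n of 191 |
|---|---|---|---|---|---|
| 0 | 1.00 | 1.000 | 1.00 | 5.0% | 191 |
| 0.01 | 1.39 | 1.195 | 1.09 | 7.3% | 137 |
| 0.02 | 1.78 | 1.390 | 1.18 | 9.6% | 107 |
| 0.05 | 2.95 | 1.975 | 1.41 | 16.3% | 65 |

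A simulation checked the levels (8,000 runs per ICC, continuous outcome, four sessions of 40 and one of 36, 196 independent controls). It gave 7.1%, 9.7% and 16.6%, and 4.9% at ICC 0.

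**Illustrative power.** Take 33% vs 20% at 191 per arm; these rates are an assumption, not the article's stated inputs. SE² = DE × 0.33 × 0.67/191 + 0.20 × 0.80/191. Power is 83% at ICC 0 and 75%, 68% and 51% at ICC 0.01, 0.02 and 0.05.

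**Number of groups.** Two groups of forty hold 2 × 40 = 80 women, which is 80/191 = 42% of the arm. Covering 191 women in forties takes 191/40 = 4.8, so about five groups.

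**The case against.** Several points on the other side stand and limit the claim.

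- **GLMM.** A reader might infer that the GLMM treats intervention women as independent, or models only repeated measures within a woman. The article does not say so. It specifies no random effects at all, and an article may leave that structure to a fuller plan. What can be said is that session is not named.
- **Sample size.** A reader might infer that the trial misses its planned power. No planned power is stated, the 33% vs 20% rates are not given as inputs, and S1 File is not shown. A design effect there cannot be fully excluded, although 196 can be reached without one.
- **Type I error.** Inflation is conditional on a positive ICC. Women, not sessions, are randomised. If the education changed nothing for anyone, sharing a session would create little or no correlation. The levels in the table apply when session effects differ but average to zero. The more usual harm is an interval that is too narrow when sessions work unevenly.
- **Facilitator.** One midwife at every session would leave no between-facilitator variance. The article is inconsistent on this, so such variance is not established.
- **Controls.** Usual care includes interactive sessions. If controls are also taught in fixed groups, the one-arm calculation does not describe the trial.
- **Two sessions.** The wording may mean two sittings per group and not two groups. In that case the number of groups is simply not stated.

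These points do not remove the core. The t-tests for six scores are prescribed and assume independent women, the sample size as described carries no clustering allowance, and group delivery in forties is fixed.

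**Conclusion.** The point holds in conditional form. The education is given to interactive groups of forty, while the sample size as described and the independent t-tests make no allowance for session clustering and the GLMM as described does not name session. If session-mates' outcomes are positively correlated, an analysis without a session term understates the SE by a factor of 1.09 to 1.41 over assumed ICCs of 0.01 to 0.05, and a nominal 5% test runs at about 7% to 16%. This rests on groups of 40, clustering in the intervention arm only, a two-sided test and an ICC range that the documents do not supply. The power figures are illustrations only. The description of the sessions needs reconciling in any case, because session cannot be modelled until the number and composition of groups are known. The change should be made, and the timing allows it: the Study process section places all follow-up visits in the future.

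**What to change.** 1. Record the education session for each intervention woman. The Implementation section already has staff tell participants their session date at allocation, so this is one variable.
2. Fit the GLMM as a partially nested model: a random session effect in the intervention arm, each control woman as her own group, a woman-level random effect for the repeated measures, and a small-sample degrees-of-freedom correction such as Satterthwaite. Add a session effect in the control arm only if controls are also taught in fixed groups.
3. Use this model in place of the independent t-tests for the score comparisons.
4. Report the ICC for the primary outcome and each score.
5. State that 196 per arm as described carries no clustering allowance, and show its sensitivity to a range of ICCs. Enrolment is complete at 382, so this informs interpretation and not recruitment.
6. Reconcile the passages on sessions: say how many groups of forty there are, how many sittings each group has, and whether one or several midwives facilitate.

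The cost is one recorded variable, one random term and a protocol amendment, for which the article provides a route. The downside is somewhat wider intervals and an imprecise session variance with only about five groups.
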